**Restorative play**			
	Resting	Taking a mental break or rest	
	Retreat	Remove themselves to a small, controlled space, may watch others	
	Reading	Reading or writing for pleasure or listening to others or music	
	Onlooking	Child deliberately steps back from nearby play for a period of observation	
**Digital play**			
	Device	Playing with or on a digital device with no interaction with the environment	
	Augmented	Using a digital device to augment their interaction with the physical world	
	Embedded	Interacting with digital prompts or devices embedded in the environment without a personal digital device	
**Nonplay**			
	Self-care	Taking care of themselves or their appearance, can include helping another with these activities	
	Nutrition	When a child is taking a break to eat or drink	
	Distress	When a child is disengaged from play and exhibiting signs of distress	
	Aggression	Refers to nonplayful, antagonistic interactions with another child or adult	
	Transition	Nonplayful movement from one space to another, no active engagement or exploration of the environment	
	Other	Other types of observed “nonplay” activities, can include “chores” or cleanup work	

Collected variables within the observational behavior mapping protocol.
**Variables and levels**
Sex: male, female, and unknownPlay type (see Table 2 for subtypes): physical, imaginative, bio, restorative, exploratory, play with rules, expressive, digital, and nonplayRisk-taking behavior: risk avoidance, exploratory risk appraisal, low or no risk, low-risk positive, low-risk negative, moderate-risk negative, moderate-risk positive, high-risk negative, and high-risk positivePlay communication: play, environment, peer-social, adult-social, cowabunga!, self-talk, could not hear, ask for help, none, and otherAdult interaction: no adult present, observing, participating, directing, restricting, and otherPhysical activity intensity: stationary or motionless, stationary with limb or trunk movements, slow or easy movement, moderate movement, and fast movementPeer interaction: solitary, parallel, cooperative, onlooking, unoccupied, and conflictGroup size: open textEnvironmental interaction: fixed manufactured, fixed natural, loose manufactured, loose natural, and narrative textInteracted with coder: yes and noAdult says *Be careful*: yes and noOpen coding: open text

#### Additional Outcome Measures

##### Attitudes Toward Outdoor Risky Play

The effect of the intervention on ECEs’ tolerance of risk in play will be assessed using the Teacher Tolerance of Risk in Play Scale [51]. The Teacher Tolerance of Risk in Play Scale is a 25-item instrument that has been validated for use as a measure of intervention effects aimed at increasing children’s access to risky play (a fundamental component of outdoor play) [51]. This measure will be administered to all ECEs at the 8 study sites during all data collection phases (times 1, 2, and 3).

##### Quality of ECEC Outdoor Spaces

The Seven Cs framework will form the basis for the assessment of outdoor space quality at all ECEC sites and the reassessment of the environment at ECEC sites after implementation of the PRO-ECO intervention and will guide the development of the plan for modification of the outdoor environment [52]. The Seven Cs framework was designed to provide guidance in the design of outdoor play spaces for children in early childhood settings based on 7 criteria: character, context, connectivity, change, chance, clarity, and challenge [52]. The Seven Cs assessment tool for ECECs will be used for baseline and postintervention measurement [53].

##### Acceptability of the PRO-ECO Intervention

As this study pilots an outdoor play intervention that can be replicated at other ECECs, it is imperative to assess the process of intervention implementation and acceptability (from the perspective of ECEs, parents, and YMCA GV managers). In this study, acceptability relates to the willingness of individuals (ECEs, parents, and children) and the organization (YMCA GV) to participate in the intervention, inform future recommendations, and apply the intervention for future use. Qualitative data will be collected before and after the intervention to understand the acceptability of the PRO-ECO intervention by the target populations at each site. Focus groups and individual key informant interviews will be organized with ECEs and ECEC administrators, who can provide critical and reflective information about the acceptability of the intervention. To understand parents’ perceptions of the acceptability of the PRO-ECO intervention, a purposive sample of parents will be engaged to participate in intercept interviews. The intercept interview method provides a convenient way of interviewing the target population at the time and location most relevant and convenient in the context of the study [54]. In our study, it will be at the time of child drop-off or pick-up at their ECEC. Intercept interviews will be approximately 10 minutes long to accommodate parents’ busy schedules.

Semistructured interview guides have been developed for the focus groups, key informant interviews, and intercept interviews with parents. These interview guides were developed by theorizing the constructs of acceptability in our study [55], such as perceived change in children’s outdoor play because of the intervention, feasibility for broad implementation, and the cost-benefit of the intervention. Focus groups will be administered to discuss children’s outdoor play, the challenges they are experiencing, and their suggestions for change, including modifications to the outdoor space. Qualitative methods will be administered at time 1 (baseline) for all sites, at time 2 for intervention ECECs, and at time 3 for wait-list control ECECs.

##### Economic Evaluation of the PRO-ECO Intervention

An economic evaluation will examine the costs of implementation of the intervention and the cost versus benefits of the PRO-ECO intervention. YMCA GV administrative data that can be monetized will be collected to consider the monetary benefits of the PRO-ECO intervention in comparison with the capital costs of intervention administration. Information will be collected throughout the study (Textbox 2) to compile a comprehensive economic evaluation guided by the framework by Levin and Schwartz [56].

An additional economic analysis will also consider the resources and costs associated with expanding the PRO-ECO intervention to future ECEC sites.

Information collected throughout the study to compile a comprehensive economic evaluation.
**Information for economic evaluation**
Ongoing administrative costs specific to the PROmoting Early Childhood Outside (PRO-ECO) intervention in both the introduction and maintenance phases (ie, beyond usual early childhood education center [ECEC] programming costs):Capital costs of using, maintaining, and staffing ECECsOut-of-pocket ECEC expensesEarly childhood educator (ECE) and manager time commitmentECE sick daysECEC staff turnoversChildren’s attendance ratesReported incidents of challenging child behaviorsReported incidents of child injuriesBenefits of the PRO-ECO intervention (outdoor play proportion)Implementation costs of the PRO-ECO intervention components:ECE training (eg, total hours spent training and average hourly pay of trainers)Built environment modifications (eg, supply costs, total hours spent purchasing supplies, total hours spent designing built environment modifications, total hours spent modifying the built environment, and average hourly pay of all parties involved)Parent engagement (eg, total hours spent engaging with parents and average hourly pay of trainers)Additional outdoor gear for children and ECEs (eg, jackets, boots, and rain ponchos)

##### Child Health, Development, and Well-being

The psychosocial strengths of children will be assessed using the Strengths and Difficulties Questionnaire, teacher version [57], which includes 25 items across 5 scales measuring emotional symptoms, conduct problems, hyperactivity or inattention, peer relationship problems, and prosocial behavior. When combining the subscales without the prosocial scale, a total difficulty score is provided to outline psychosocial challenges and strengths [58]. In addition, ECEs’ perceptions of children’s confidence, motivation, knowledge, and understanding of outdoor play participation will be captured through ECEs’ pedagogical narratives, focus groups, and interviews. Children’s physical activity intensity will be measured using the Children’s Activity Rating Scale (CARS) as part of the OBM protocol [59]. Injury incidents will be measured through the abstraction of data from ECEC incident report forms. The Preschool Social Behavior Scale-Teacher Form [60] will be used to measure child development and behavior outcomes, including 19 items measuring relational aggression, overt aggression, prosocial behavior, and depressed affect. Child health, development, and well-being outcomes will be assessed at baseline (time 1), 6-month follow-up (time 2), and 12-month follow-up (time 3).

#### Study Covariates

Covariates for this study will include demographic information of children, including sex, age, first language spoken at home, family composition, average household income, and the highest level of education completed by a household member. The demographic information of the children will be collected using parent-reported questionnaires. In addition, the child’s length of time at the ECEC and other forms of formal care, as well as the type of care (full-time or part-time), will be collected. At the time of data collection, data on the weather, temperature, and time of day will be recorded. The study covariates will be collected at each data collection time point (time 1, time 2, and time 3).

The following information related to recruitment, retention, and attendance will be collected throughout the intervention period (1 year) for both the intervention and control sites: (1) number of eligible children that were approached to participate in the study; (2) number of children who consented to participate, did not consent to participate, or did not respond; (3) number of children who withdrew from the study; (4) number of children who enrolled in the ECECs after initiation of the intervention; (5) number of children who left the ECEC after initiation of the intervention; and (6) individual and center-wide attendance rates at each ECEC. An overview of outcome variables measured as part of the PRO-ECO study is shown in Table 3.

**Table 3 table3:** Outcome variables and measures for the PROmoting Early Childhood Outside (PRO-ECO) study^a^.

Outcome, subcategory, and variable				Measure		Informant						
						Child		ECE^b^		ECEC^c^		Parent
**Primary outcomes—children**												
	Occurrence of outdoor play		TOPO^d^—play type		✓							
	Diversity of outdoor play behavior		TOPO—play type		✓							
**Additional outcomes**												
	**ECEC**											
		Quality of ECECs’ outdoor play space	Seven Cs ECEC assessment score						✓			
		ECEs’ attitudes toward risky play	T-TRiPS^e^				✓					
		Acceptability of PRO-ECO intervention	Interviews and focus groups with ECEs and administrators; intercept interviews with parents				✓				✓	
		Economic analysis of PRO-ECO intervention	ECE and child attendance, ECE staff turnover, incidents of children’s challenging behaviors, institution and intervention costs, and nonfinancial outcomes (outdoor play)				✓		✓			
	**Child health, development, and well-being**											
		Psychosocial	SDQ^f^		✓							
		Injury	Reported incidents						✓			
		Physical activity intensity	OBM^g^ (CARS^h^)		✓							
		Development and behavior outcomes	PSBS-T^i^				✓					

^a^All variables will be collected at each time point (time 1, time 2, and time 3).

^b^ECE: early childhood educator.

^c^ECEC: early childhood education center.

^d^TOPO: Tool for Observing Play Outdoors.

^e^T-TRiPS: Teacher Tolerance of Risk in Play Scale.

^f^SDQ: Strengths and Difficulties Questionnaire.

^g^OBM: observational behavior mapping.

^h^CARS: Children’s Activity Rating Scale.

^i^PSBS-T: Preschool Social Behavior Scale-Teacher Form.

### Analysis

#### Primary Outcome Analysis

The proportion of play occurrence in comparison with nonplay occurrence across ECECs at baseline will be summarized by intervention group using frequency and percentages. This follows a similar analysis completed by van Dijk-Wesselius et al [61], who used a comparison of children’s play and nonplay behavior before and after the intervention as an effective and significant measurement outcome of children’s outdoor play occurrences. The frequencies and percentages of all play types will also be summarized by treatment group to provide a descriptive overview of diversity of play. This follows previous descriptive analyses completed by Loebach et al [48,62], who used OBM data to examine the frequency and diversity of play types. Baseline demographic and ECEC characteristics will be summarized by group using mean and SD and median and IQR for continuous variables, and frequencies and percentages for categorical characteristics. Bivariable relationships between children’s demographic characteristics and outdoor play occurrence, as well as by intervention group, will be explored to assess for potential confounding at an individual level given that randomization is at the cluster level. Mixed effect models will be used to assess differences in quantitative outcome measures between the intervention and wait-list control groups as well as within-group comparisons of pre- and postintervention measures.

#### Cost-benefit Analysis

Cost-benefit analyses aim to estimate the costs and benefits of a particular policy or program and determine whether the societal impacts are worth the investment. For both short- and long-term cost-benefit analyses, we will (1) estimate the economic values of the costs and benefits for the a priori variables of interest (capital costs and changes in occurrence of outdoor play) and (2) apply an investment criterion to the estimated values of costs and benefits [63]. Our analysis framework will be based on decades of published methods from economists evaluating the Perry Preschool project [64-67], a longitudinal study that followed preschool-aged children from disadvantaged backgrounds through adult life [63,68]. To assess societal effects, we will use a net present value criterion to account for benefits and costs that vary over time [63]. For the cost-effectiveness analysis, we will examine differences in outdoor play occurrences per dollar spent on the PRO-ECO intervention versus traditional outdoor play delivery [69].

#### Qualitative Analysis

Qualitative interview data from ECE focus groups, individual key informant interviews, and intercept interviews with parents will be analyzed using the qualitative content analysis method [70]. Theorized constructs of acceptability, which inform our interview guides, will also be used as the analytical framework to understand and categorize participant narratives. Given that the primary aim of the qualitative interviews is to describe participants’ acceptability of the intervention, this deductive analytical approach will serve well in providing focus and content for different constructs of our interest. New concepts will also be constructed that are not fully captured or described by the existing analytical framework, and concepts that are deemed necessary for further exploration will be analyzed anew using the thematic analysis method [71]. More specifically, we will follow 6 phases of reflexive thematic analysis—*familiarization, generating initial codes, searching for themes, reviewing themes, defining and naming themes, and producing the reports*—to go beyond descriptive reports and yield a more complex and nuanced account of a phenomenon or experience.

### Ethics Approval

Ethics certification was received from the University of British Columbia and the Children’s and Women’s Health Centre of British Columbia Research Ethics Board (H20-03912).

## Results

This study was developed to implement and evaluate the PRO-ECO intervention. Funding to conduct this study was confirmed in January 2021. Ethics approval through the University of British Columbia and the Children’s and Women’s Health Centre of British Columbia Research Ethics Board was received in March 2021, and participants were recruited beginning in August 2021. Baseline data were collected from October 2021 to November 2021, and the intervention ECEC sites received the PRO-ECO intervention in December 2021. As of April 2022, a total of 130 children have been recruited to participate in this study.

## Discussion

### Overview

This study is novel in building and evaluating a comprehensive intervention to enhance outdoor play in Canadian ECECs. The PRO-ECO intervention addresses ECECs’ socioecological context, including the ECEs’ individual knowledge, attitudes, and behaviors; parents’ knowledge and attitudes toward outdoor play; the quality of the outdoor play space; and the policies governing the facility. The intervention is underpinned by social cognitive theory using evidence-based behavior change techniques to foster change. It includes aspects that can be universally applied but also the flexibility to tailor to local needs and context. Using a mixed methods, wait-list control cluster randomized trial design, the implementation and efficacy of the PRO-ECO intervention can be assessed.

The results and lessons learned through this study will inform the feasibility of a full-scale randomized trial that continues to assess the effectiveness of the intervention as well as help develop guidelines for the implementation of the PRO-ECO intervention in other ECECs. Furthermore, the health economic analyses will generate data to inform the sustainability of future academic and health policies in ECECs.

### Strengths and Limitations

A strength of this study and the development of the PRO-ECO intervention is that an interdisciplinary stakeholder committee has been gathered to inform best practices and the primary components of this intervention. The process has included extensive partnership and consultation with YMCA GV management; ECEs; licensing officers; and multidisciplinary experts in early childhood education, landscape architecture, public health, outdoor play, and child development.

The PRO-ECO study will provide evidence-based information on the curriculum, policies, outdoor environments, and professional development training that support outdoor play opportunities among children in ECECs. The results of this study may be applied broadly through the expansion of the intervention to other YMCA ECECs and potentially other child care programs across Canada. This study will also provide insightful alignment with ongoing international research on outdoor play in ECECs, such as a recent study published in Norway [27] and research in Washington on their newly licensed outdoor ECEC programs [72].

In designing the PRO-ECO study, the research team identified common challenges when implementing an outdoor play intervention in ECECs and aimed to address them in the study design. However, because of the complexity of this study design, there are limitations that are anticipated throughout this study. First, the PRO-ECO intervention is a pilot study and, therefore, the sample size is based on feasibility while retaining optimal statistical power. To understand if the PRO-ECO intervention can be administered and assessed in a larger sample size, a sample of 8 ECECs is included in this study. This sample size could limit the identification of our estimated effect size between the intervention and control groups. The site inclusion criteria consider the readiness of the site to participate and the geographic area where the site is located. In addition, stratified randomization strives to create an intervention and control group that are similar while also ensuring there is a diverse representation of child care sites in the Greater Vancouver region. However, although considerations were made to create a diverse and representative sample of child care sites, we cannot account or stratify for all site characteristics.

Although this study strives to measure change in the occurrence of outdoor play before and after the intervention in comparison with nonplay, there is a possibility that the amount of *nonplay* at baseline is already low and would be difficult to reduce further. In this case, it may not be possible to detect a significant increase in the occurrence of outdoor play after the implementation of the intervention. Examining diversity of play as an additional primary outcome measure will provide more information to understand changes in outdoor play frequencies before and after the intervention and inform play measures for future studies. The CARS is a direct observation method used to measure physical activity levels among children and was selected based on the financial resources available for this study. In comparison with the use of indirect calorimetry, accelerometry, and heart rate monitoring to measure children’s physical activity levels, the CARS may be subject to measurement error. However, all researchers collecting these data were extensively trained on the use of this tool, and previous studies have validated the use of direct observation methods, including the CARS, to assess children’s physical activity [73].

Postintervention data collection will occur 1 year after baseline. It is expected that some children will be lost to follow-up as a result of leaving the ECEC or withdrawing consent. As indicated earlier, primary variable data will be collected at the center level, allowing us to study ECECs rather than individual children. Although the children participating in this study may change, we will engage additional children for postintervention data collection as needed. We anticipate study contamination between sites as ECEs can be moved between sites to accommodate staffing shortages. Furthermore, the champions at each site attend a weekly PRO-ECO project meeting where logistics are discussed and would be aware of the general activities involved in implementing the PRO-ECO intervention.

In addition, the design of this study commenced in 2019, before the COVID-19 global pandemic. Although ECECs continue to function and provide essential care to many families, we recognize that this has caused changes in the delivery of education and care across Canada. Disruption related to enrollment rates, staffing, or outdoor play practices at ECECs may cause limitations to participation and data collection in our study.

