### Study Objectives

The PRO-ECO study is guided by the following objectives: (1) to develop and implement the pilot PRO-ECO intervention with overarching components common to all ECEC intervention sites as well as customizable components that are responsive to the needs of each ECEC, (2) to assess the efficacy of the PRO-ECO intervention in increasing and diversifying outdoor play behavior in children aged 2.5 to 6 years, and (3) to assess the acceptability of the PRO-ECO intervention.

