### Study Design

This study is a pilot wait-list control cluster randomized trial (trial registration NCT05075580) with an intervention arm and a wait-list control arm (Figure 1). A mixed methods approach will be used to collect qualitative and quantitative data designed to meet the study objectives. Quantitative outcomes support the evaluation of the primary outcome variables, and qualitative data assess the acceptability of the implementation of the intervention. Qualitative data will be collected concurrently with quantitative data and allow researchers to explore how the participants experience the intervention.

The study will be conducted in 8 ECECs operated by the YMCA of Greater Vancouver (YMCA GV) from September 2021 to November 2022. Individual ECECs served as the unit of randomization, with 50% (4/8) intervention sites and 50% (4/8) wait-list control sites composing the final sample. Intervention sites received the intervention immediately following baseline data collection, whereas wait-list control sites will receive the intervention 6 months later. Data on outcome measures will be collected at 3 time points: baseline (time 1), 6-month follow-up (time 2), and 12-month follow-up (time 3). Thus, outcome data will assess short- and longer-term outcomes within the intervention group and short-term outcomes within the wait-list control group. Baseline and postintervention data collection will occur during the fall and spring to ensure similar weather patterns at all time points.

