#### Sample Size

This study will produce preliminary data for the calculation of a sample size for future studies [40]. Therefore, the sample size for this study is based on the feasibility of the pilot study. Recruitment for this study occurred during the COVID-19 pandemic, and many ECECs were operating with reduced enrollment. A total of 157 children were enrolled in participating ECECs and invited to participate, of whom 82 (52.2%) participated in the intervention arm and 75 (47.8%) participated in the wait-list control arm. Across all 8 ECECs, 82.8% (130/157) of children consented to participate in baseline data collection.

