### Data Collection and Measures

#### Primary Outcomes

The primary trial outcome is the occurrence of outdoor play behavior at ECECs during designated outdoor play times. Play behavior is coded using the expanded version of the Tool for Observing Play Outdoors (TOPO) developed by Loebach and Cox [46] and captured using a systematic observational mapping protocol. The TOPO measures children’s play behavior through validated categories of 8 play types and 1 nonplay type along with their corresponding subtypes (Table 2). For this study, we will code play behavior and nonplay behavior at the subtype level at each ECEC, with all play types being categorized as *Play* and all nonplay types being categorized as *Nonplay* for the analysis of our primary outcome. In addition, diversity of children’s outdoor play behavior will be examined using proportions of different play types.

The TOPO is implemented using a place-based observational behavior mapping (OBM) protocol. OBM strives to understand how an environment supports movement and use behaviors by mapping, recording, organizing, displaying, and analyzing geographically located data [47,48]. Base maps are used to provide an overview of the given environment, and predetermined observable data variables are collected. Each ECEC outdoor play space was divided into 2 measurement zones. In total, 2 researchers (one in each zone) will conduct observations at each ECEC as children participate in designated outdoor play time as determined by the ECEC. Researchers will scan each zone in a counterclockwise direction selecting the first child to enter the viewpoint. The researchers will then capture a 15-second video of the child’s outdoor play and assign play behavior data to the primary activity performed during the video. A total of 200 fifteen-second play events will be compiled and coded for each ECEC site at each data collection time point (time 1, time 2, and time 3). The observational data will be collected using a place-centered approach that captures play behaviors of a range of children across the *space* of the ECEC rather than a person-centered approach that focuses on individual children. During each observation period, if there is no child in a given observational zone, a note will be made to indicate that no child was playing in that zone at that time. Additional variables will be collected through OBM and are outlined in Textbox 1.

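### The article says its feasibility-based sample of eight sites keeps its power, but shows no calculation for this and contradicts it elsewhere

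*Protocol article*

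**What the plan says.** The protocol article speaks to sample size and power in two places.

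- **Sample Size (Methods):** "the sample size for this study is based on the feasibility of the pilot study". The same section gives the purpose: "This study will produce preliminary data for the calculation of a sample size for future studies".
- **Strengths and Limitations (Discussion):** "the sample size is based on feasibility while retaining optimal statistical power". Two sentences later: "This sample size could limit the identification of our estimated effect size between the intervention and control groups".

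The design facts that bear on power are in Study Design and Primary Outcomes. "Individual ECECs served as the unit of randomization", with "50% (4/8) intervention sites and 50% (4/8) wait-list control sites composing the final sample". On measurement: "A total of 200 fifteen-second play events will be compiled and coded for each ECEC site at each data collection time point". Objective 2 is worded as a test of efficacy: "to assess the efficacy of the PRO-ECO intervention in increasing and diversifying outdoor play behavior". The Abstract and the Primary Outcome Analysis section plan mixed effect models that use baseline and postintervention data and allow for the clustering.

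The article gives no significance level, power target, between-site SD, intraclass correlation or numerical effect size.

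**The concern.** A statement that power was retained is a positive claim about the design, and the rest of the article does not bear it out. A size set by what was feasible, in a study meant to supply the inputs for later sample-size work, has not been shown to have any particular power. The same paragraph then warns that the size may be too small to pick up the effect.

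The claim also sits beside an efficacy objective and a planned between-arm comparison. A reader who takes it at face value would give a non-significant result more weight than eight randomised sites can carry, including when a full-scale trial is being considered.

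**Working it through.** **1. Is there a figure to reproduce?** No. The article attaches no number to its power statement, so the check has two parts: whether the text is consistent, and what a 4 v 4 design can detect under stated assumptions.

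**2. Consistency of the text.** Sample Size names feasibility alone. Strengths and Limitations names feasibility plus retained power, then says the size could limit identification of the effect. The first and third statements agree with each other; the power clause fits neither.

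**3. Inputs for the calculation.**
- From the article: 4 sites per arm, with the site as the unit of randomisation; 200 coded events per site and time point.
- Assumed, because the article does not give them: two-sided 5% level, 80% power, and the difference d expressed in SDs of site-level means. That SD includes the sampling noise from 200 events, so the number of clips is already inside it. More clips could shrink the SD but would not add randomised units.

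**4. Unadjusted comparison of site means.** The degrees of freedom are 4 + 4 − 2 = 6, and the critical t value is 2.447. The noncentrality is d × √(n/2) = d × √(4/2) = 1.414 d. Power is the probability that a noncentral t variable on 6 df falls beyond ±2.447.

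| Difference d (SD) | Power |
|---|---|
| 0.8 | 16% |
| 1.0 | 22% |
| 1.5 | 43% |
| 2.0 | 66% |
| 2.38 | 80% |
| 2.77 | 90% |

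So 80% power needs d = 2.38. Sensitivity at 80% power:
- One-sided 5% on 6 df: 2.00.
- Two-sided on 5 df: 2.49.
- Two-sided on 4 df: 2.66.
- Normal approximation: (1.960 + 0.842) × √(2/4) = 1.98, which is too optimistic with eight clusters.

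**5. With baseline adjustment.** The planned models use baseline data, so the unadjusted figure is not the whole answer. One baseline covariate leaves 5 df, for which d at 80% power is 2.485 in residual SD units. Adjustment multiplies the SD by √(1 − r²), where r is the correlation between baseline and follow-up site means. The detectable difference is therefore 2.485 × √(1 − r²). Power at 0.8 SD uses the effective difference 0.8 / √(1 − r²) on 5 df.

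| Assumed r | √(1 − r²) | Detectable difference (SD) | Power at 0.8 SD |
|---|---|---|---|
| 0.5 | 0.866 | 2.15 | 19% |
| 0.7 | 0.714 | 1.77 | 25% |
| 0.8 | 0.600 | 1.49 | 34% |
| 0.9 | 0.436 | 1.08 | 55% |

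Even at r = 0.9, 80% power needs a difference of more than one SD of site-level means.

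**The case against.** The strongest reply is that the limitation is already disclosed. The power clause sits in a list of limitations, and the paragraph goes on to warn about sample size. The next part of the same section warns that a ceiling on play may make an increase undetectable. The Sample Size section and the Discussion overview frame the study as groundwork for a larger trial. This stands, and it limits the weight of the point. A reader might infer that a null result will be taken as proof of no effect; with those caveats in print, that is a risk and the documents do not support calling it more.

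A second reply is that the clause names no target, so it could mean the best power available within feasibility, and no calculation can refute that. This also stands in part. The fault is that the clause is unsupported and at odds with the surrounding text. The arithmetic shows how far the design is from conventional power for moderate differences; it does not disprove a stated figure.

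Third, 2.4 SD describes an unadjusted comparison, which is not the planned analysis. This is correct, and it is why a range is given. Quoting 2.4 alone would overstate the problem if baseline and follow-up site means are strongly correlated.

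Finally, a reader might fault the article for mentioning an estimated effect size without giving its value. That value may be in the full protocol or the SAP, which are not shown, and a condensed article may omit it. It is not part of this point.

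**Conclusion.** Wrong as written, minor weight. The article asserts a power property that it does not support and that its own text contradicts. Under the assumed two-sided 5% level and 80% power, four sites per arm can detect about 2.4 SD of site-level means unadjusted, or about 2.2 down to 1.1 SD with baseline adjustment at correlations of 0.5 to 0.9. Power for a difference of 0.8 SD is between 16% and 55% over that span.

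The inconsistency in the text depends on no assumption. The numbers depend on the significance level, the power target, the t approximation for site means and the baseline correlation, none of which the article gives. The design itself is not at fault: a pilot may be sized on feasibility, provided that it is described that way.

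**What to change.** In Strengths and Limitations:
- Delete the clause about retaining power and leave feasibility as the stated basis, in line with the Sample Size section.
- Keep the existing sentence that the size could limit identification of the effect, including its mention of an estimated effect size.
- Add the detectable difference with its assumptions. For example: with four sites per arm, a two-sided 5% test and 80% power, the study can detect about 2.4 SD of site-level means unadjusted, and about 2.2, 1.8, 1.5 or 1.1 SD with baseline adjustment if the baseline correlation is 0.5, 0.7, 0.8 or 0.9.

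For objective 2, report the between-arm effect as an estimate with a 95% interval, and state that a non-significant result from this pilot is not evidence of no effect.

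The cost is wording only, with no additional sites, children or observations. The stated property of the design becomes less favourable.
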